# Effect of 12-week intermittent calorie restriction compared to standard of care in patients with nonalcoholic fatty liver disease: a randomized controlled trial

**DOI:** 10.1186/s13063-023-07444-4

**Published:** 2023-08-02

**Keywords:** Nonalcoholic fatty liver disease, Nonalcoholic steatohepatitis, Intermittent calorie restriction, Steatosis, Fibrosis, MRI-proton density fat fraction, Elastography, Weight reduction, Dietary therapy

## Abstract

**Background:**

Nonalcoholic fatty liver disease (NAFLD) is the most common cause of chronic liver disease. NAFLD can result in various complications. Owing to the lack of effective pharmacological therapies, lifestyle modifications are the cornerstone treatment for NAFLD. However, there has been no recommendation for a specific dietary therapy. Because no significant effects have been observed in previous studies. Intermittent calorie restriction (ICR) consists of alternating phases of extreme energy restriction and regular energy intake. Recent studies have demonstrated a significantly higher reduction in liver fat content in the ICR group than in the standard of care (SOC) or continuous calorie restriction groups in patients with NAFLD. However, critical weaknesses limit the broader application of ICR in clinical practice; those are a lack of appropriate assessment tools, different cutoffs of body mass index (BMI) used to define obesity, and different food portions. Thus, we report a protocol for a prospective, randomized controlled trial. The trial will evaluate the effect of 12-week ICR on improving liver fat content in NAFLD patients (Nonalcoholic Fatty Liver Disease-Intermittent Calorie Restriction [FLICR]).

**Methods:**

We will include adult (19–75 years) NAFLD patients. NAFLD will be diagnosed by histologic assessment or magnetic resonance imaging-proton density fat fraction (MRI-PDFF) ≥ 8%. A total of 72 patients will be classified according to BMI (obese group: BMI ≥ 25 kg/m^2^ [*n* = 36] and non-obese group: BMI < 25 kg/m^2^ [*n* = 36]). Participants will be followed up for 24 weeks. Participants will be randomly assigned to one of the two groups: the SOC or ICR group. The primary objective will be the change in liver fat content measured using MRI-PDFF from baseline to 12 weeks.

**Discussion:**

This FLICR study may provide clinical evidence on ICR in the treatment of NAFLD in both obese and non-obese patients. The use of ICR in patients with NAFLD will improve the clinical outcomes of patients facing a shortage of effective medical therapy.

**Trial registration:**

This trial was registered at the United States National Library of Medicine (NLM) at the National Institutes of Health. ClinicalTrials.gov NCT05309642. Registered on April 4, 2022.

**Supplementary Information:**

The online version contains supplementary material available at 10.1186/s13063-023-07444-4.

## Introduction

### Background and rationale

Nonalcoholic fatty liver disease (NAFLD) is the most common cause of chronic liver disease worldwide, affecting approximately 25% of the world’s population [1]. In Korea, the prevalence of NAFLD has been reported from 20 to 30% [2]. The broad spectrum of NAFLD encompasses simple hepatic steatosis to nonalcoholic steatohepatitis (NASH), which can progress to cirrhosis in 15–20% of affected patients, as well as the development of hepatocellular carcinoma (HCC) and death [3, 4]. NAFLD is an independent risk factor for the development of various extrahepatic diseases, including cardiovascular disease (CVD) and malignant tumors [2].

Therefore, proper and active management is required to reduce intrahepatic inflammation and fibrosis and to treat comorbid metabolic diseases in patients with NAFLD. However, because effective pharmacological therapies for NAFLD have not yet been approved, non-pharmacologic therapies including weight reduction through dietary control and exercise are the cornerstone treatment for both obese and non-obese NAFLD patients, based on the results of previous studies [5–7].

Although recent studies have evaluated the association between specific nutrients or dietary habits including low carbohydrate/high-fat diet or intermittent fasting and the development or progression of NAFLD, these studies have been conducted on only a small number of patients, and few have shown significant improvement in hepatic inflammation or fibrosis [8–12]. Intermittent calorie restriction (ICR), comprising phases of extreme energy restriction and regular energy intake, is a novel dietary approach for NAFLD treatment [13]. Significantly higher reductions in liver steatosis with ICR than with the standard of care (SOC) or continuous calorie restriction (CCR) have been reported in NAFLD patients [14–17]. Although promising findings have been reported in previous studies of 6–12 weeks of dietary intervention, the lack of appropriate assessment tools, different cutoffs of body mass index (BMI) used to define obesity, and different food portions between studies are the major limitations [14–17].

### Objectives

Therefore, we hypothesized that ICR would be effective in reducing liver fat content measured using magnetic resonance imaging-proton density fat fraction (MRI-PDFF) compared to SOC in patients with NAFLD. Finally, we developed a prospective, randomized controlled trial (RCT) to evaluate the effect of 12-week ICR on improving liver fat content in NAFLD, stratifying patients into obese and non-obese groups.

### Trial design

The Nonalcoholic Fatty Liver Disease-Intermittent Calorie Restriction trial was designed as a prospective, two-arm, open-label RCT to investigate the efficacy of 12-week ICR in reducing liver fat content in NAFLD patients.

## Methods: participants, interventions, and outcomes

### Study setting

The study will recruit 72 patients who will be followed up actively according to the protocol for 24 weeks. Patients will be classified according to their BMI (obese group: BMI ≥ 25 kg/m^2^ [36 patients] and non-obese group: BMI < 25 kg/m^2^ [36 patients]). An enrollment period of 12 months is expected.

### Eligibility criteria

The following are the inclusion criteria:NAFLD diagnosed by (1) histologic assessment with a fat accumulation of > 5% of the liver’s weight on biopsy or (2) radiologic assessment with MRI-PDFF ≥ 8%Age between 19 and 75 yearsCapability to understand the study and the individual consequences of participationSigned and dated declaration of agreement in the forefront of the study

The following are the exclusion criteria:Daily alcohol consumption > 30 g in men and > 20 g in womenOther causes of chronic liver disease (hepatitis B, C, D, and E virus infection; human immunodeficiency virus; autoimmune diseases; chronic cholestatic liver disease; drug-induced liver injury; hereditary hemochromatosis; Wilson disease; and α-1-antitrypsin deficiency)Liver cirrhosisHepatocellular carcinomaMedications that cause liver disease or secondary NAFLD (e.g., tamoxifen, systemic corticosteroids, methotrexate, tetracycline, estrogens, and valproic acid)Changes in body weight > 5% in the last 3 monthsIntake of medical treatment for NAFLD/NASH in the last 6 months (except vitamin E)DiabetesPregnancyPatients after organ transplantationMissing or lacking consent capability

### Who will take informed consent?

The investigators will be obtaining the informed consent from each study participant. Each participant must have voluntarily given informed consent and signed by the patient and an investigator before any study-specific procedures are initiated.

### Additional consent provisions for the collection and use of participant data and biological specimens

On the consent form, participants will be asked if they agree to the use of their data should they choose to withdraw from the trial. Participants will also be asked for permission for the research team to share relevant data with people from the universities taking part in the research or from regulatory authorities, where relevant. Therefore, all those additional tests will be performed only after obtaining informed consent, based on each participant’s voluntary participation and agreement to those procedures.

### Interventions

#### Intervention description

##### Active comparator (ICR arm)

On two non-consecutive days per week, participants in the ICR (5:2 diet) group will be instructed to consume 500 kcal/day for women and 600 kcal/day for men. Recipes will be provided with suggestions for meals that do not exceed calorie restrictions. For the remaining 5 days of the week, they will receive instructions and recipes that follow the Korean Dietary Reference Intakes, with an intake limit of 2000 kcal/day for women and 2500 kcal/day for men. The percentage of energy (E%) from the different macronutrients in the recipes will be 45–60 E% carbohydrates, 25 E% fat, and 10–20 E% protein.

##### Placebo comparator (SOC arm)

The SOC group will receive 80% of the standard calories (1200–1500 kcal/day or reducing 500–1000 kcal/day from standard calories). They will receive individualized guidance from a hepatologist on how to choose a healthy diet, reduce the intake of sweets and saturated fatty acids, increase sources of unsaturated fat, avoid large portions, and regularly eat three meals per day. Sample meal plans by calorie intake are presented in Supplementary materials.

#### Criteria for discontinuing or modifying allocated interventions

Patients may be discontinued from the study at any time if, in the opinion of the investigator, it is medically necessary or if it is an expressed wish of the patient. The patients are free to discontinue their participation in the trial at any time.

#### Strategies to improve adherence to interventions

Study visits will be performed at baseline and every week during the intervention period (telephone consultation with 24-h recall or visit to the clinic with a 3-day diet diary).

#### Relevant concomitant care permitted or prohibited during the trial

At baseline visit (0 weeks), the exercise practitioner will conduct exercise consultation and educate enrolled participants to do at least moderate-intensity exercise for more than 30 min more than 3 times per week throughout the trial period.

#### Provisions for post-trial care

N/A

### Outcomes

The primary objective is to evaluate the impact of ICR on liver steatosis measured using MRI-PDFF (time frame: baseline and 12 weeks), and the outcome of interest is a change in the MRI-PDFF value of at least 30% with ICR. Secondary objectives include changes in liver fibrosis by MRE (time frame: baseline and 12 weeks); anthropometrics including BMI (kg/m^2^) (time frame: baseline, 12 and 24 weeks); BCA measured using InBody (time frame: baseline, 12 and 24 weeks); VAT measured using fat computed tomography (CT) (time frame: baseline, 12 and 24 weeks); QOL score measured using Chronic Liver Disease-NAFLD Questionnaire (CLDQ) (time frame: baseline, 12 and 24 weeks); hormones including leptin, adiponectin, ghrelin, GLP-1, apelin, chimerin, and osteopontin (time frame: baseline and 12 weeks); liver metabolites including diglycerides, fatty acid, phosphatidylethanolamines, phosphatidylcholines, methionine, S-adenosyl-l-methionine, and methylthioadenosine (time frame: baseline and 12 weeks); and gut microbiota analyzed with 16S rRNA gene sequencing (time frame: baseline and 12 weeks). Polymorphisms of PNPLA3, TM6SF2, TM4SF5, SREBF2, MBOAT7-TMC4, HSD17B13, and adenine insertion (A-INS) will also be analyzed using next-generation sequencing (NGS). The objectives of this study are summarized in Table 1.

**Table 1 Tab1:** Objectives of the Nonalcoholic Fatty Liver Disease-Intermittent Calorie Restriction (FLICR) study

	Study time points (weeks)			
	Intervention period			Maintenance period
	0	6	12	24
**Primary objective**				
Change in liver steatosis by MRI-PDFF	■		■	
**Secondary objectives**				
Change in liver fibrosis by MRE	■		■	
Change in anthropometrics	■		■	■
Change in BCA by InBody	■		■	■
Change in VAT by fat CT	■		■	■
Change in quality of life score by CLDQ	■		■	■
Change in hormone	■		■	
Change in liver metabolites	■		■	
Change in gut microbiota by 16S rRNA gene sequencing	■		■	
Polymorphism of SNPs using NGS	■			

*MRI* Magnetic resonance imaging, *PDFF* Proton density fat fraction, *MRE* Magnetic resonance elastography, *BCA* Body composition analysis, *VAT* Visceral adipose tissue, *CT* computed tomography, *CLDQ* Chronic Liver Disease-NAFLD Questionnaire, *SNP* Single nucleotide polymorphism, *NGS* Next-generation sequencing

### Participant timeline

The patients will be followed up for 24 weeks (Fig. 1). Detailed dietary consultation will be conducted by a nutritionist at the baseline visit, and each participant will be provided with a written summary of the dietary advice. The dietary intervention will be performed during the first 12 weeks, and 12 weeks hereafter is the maintenance period, and patients will be followed up at the end of the study period. The schedule of the assessments of the study procedures is summarized in Table 2.

**Fig. 1 Fig1:**
[figure not shown]
Study timeline. ICR, intermittent calorie restriction; SOC, standard of care

**Table 2 Tab2:** The schedule of enrollment, interventions, and assessments

Time point	Study period					
	**Enrollment**	**Allocation**	**Post-allocation**			**Close-out**
	*** − t***_***1***_	***0***	***0 weeks***	***6 weeks***	***12 weeks***	***24 weeks***
**Enrollment**						
**Eligibility screen**	X					
**Informed consent**	X					
**Screening**	X					
**Allocation**		X				
**Interventions**						
*** [ICR]***			X	X	X	
*** [SOC]***			X	X	X	
**Examinations**						
***MRI-PDFF, MRE***			X		X	
***Anthropometrics***			X	X	X	X
***Blood sample***			X		X	X
***Stool, urine sample***			X		X	X

Follow-up at 12 weeks (end of treatment) will include the following mandatory tests: assessment of liver fat by MRI-PDFF, liver fibrosis by magnetic resonance elastography (MRE), anthropometrics, body composition analysis (BCA), visceral adipose tissue (VAT), food intake, quality of life (QOL), liver metabolites, microbiome, and hormones (leptin, adiponectin, ghrelin, GLP-1, apelin, and osteopontin). Follow-up will be terminated at the end of the maintenance period (24 weeks), and anthropometrics, BCA, VAT, food intake, and QOL will be assessed. All study participants, except those who withdraw consent for the study, will be followed up for the study period.

### Sample size

In a previous study, the percentage of participants who reached the endpoint of a relative reduction in liver fat content > 30% measured using MRI-PDFF after 12 weeks was 80% in the ICR group and 29% in the control group [17]. Based on this assumption, 72 participants (36 in the obese group and 36 in the non-obese group) are planned to be randomized into the two treatment groups in a 1:1 ratio (ICR:SOC) to achieve 80% power for superiority comparison (Fisher’s exact test) of the primary objective between the two treatment groups, with a two-sided type I error of 5% and allowing for a 10% dropout rate. G*Power 3.1.9.4 was used to calculate the sample size.

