### Methods for additional analyses (e.g., subgroup analyses)

Subgroup analyses will be performed according to the obese and non-obese groups.

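### 72 patients and 80% power do not belong together for the ICR versus SOC comparison: the stated inputs need 38 randomised, and 72 gives about 99%

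*Protocol article*

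**What the plan says.** The Sample size section of the protocol article takes its effect size from one earlier study. The endpoint is a "relative reduction in liver fat content > 30% measured using MRI-PDFF after 12 weeks", and the share of participants who reached it "was 80% in the ICR group and 29% in the control group". From this the section plans "72 participants (36 in the obese group and 36 in the non-obese group"), who "are planned to be randomized into the two treatment groups in a 1:1 ratio (ICR:SOC) to achieve 80% power for superiority comparison". The test is Fisher's exact test, and the comparison is named as the primary objective between the two treatment groups, "with a two-sided type I error of 5% and allowing for a 10% dropout rate".

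The BMI groups appear elsewhere in two roles. The allocation section makes BMI a stratification factor for the randomisation. The section on additional analyses says: "Subgroup analyses will be performed according to the obese and non-obese groups". Nowhere does the article say that the power calculation was done within a BMI group.

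**The concern.** An absolute difference of 51 percentage points is very large, and a two-arm comparison of that size does not usually need 72 patients for 80% power. Every input is printed in the section, so the figure can be checked directly.

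If total and power do not match, the reader does not know what the 80% describes. Someone who takes the sentence at its word will think that the pooled comparison has a one-in-five chance of missing the assumed effect, when under the stated rates it is nearer one in a hundred. Someone who guesses that the figure was meant for each BMI group may read a non-significant result in non-obese patients as coming from a test planned at 80% power, a claim that the article does not make. The Discussion gives the evaluation of ICR in non-obese patients as the reason for stratifying, so that second reading may well occur.

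**Working it through.** **Inputs, all from the Sample size section:** responder rates 0.80 (ICR) and 0.29 (control); Fisher's exact test; two-sided 5%; target power 80%; 1:1 allocation; 10% dropout; 72 randomised, 36 per BMI group.

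**Method.** For n per arm, exact power is the sum over all outcomes (i, j) of Bin(i; n, 0.80) × Bin(j; n, 0.29), counting only the tables with a Fisher p-value of at most 0.05.

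**Step 1: try to reproduce 72 at 80% power.**

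- Fisher, exact: 16 per arm gives 76.1% and 17 per arm gives 81.1%. So 34 evaluable are needed, and 34 / 0.9 = 37.8, that is 38 randomised.
- Normal approximation: n = [1.96 × √(2 × 0.545 × 0.455) + 0.8416 × √(0.80 × 0.20 + 0.29 × 0.71)]² / 0.51² = (1.380 + 0.509)² / 0.2601 = 13.7, so 14 per arm; 28 / 0.9 = 31.1, that is 32 randomised.
- The same with continuity correction: (13.72 / 4) × [1 + √(1 + 4 / (13.72 × 0.51))]² = 17.4, so 18 per arm; 36 / 0.9 = 40 randomised.

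A single comparison therefore needs 32 to 40 randomised. None of these variants comes near 72.

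**Step 2: power that 72 gives for the comparison named.** After dropout, 72 × 0.9 = 64.8, or about 32 per arm.

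| Evaluable per arm | Exact Fisher power, 80% vs 29% |
|---|---|
| 32 | 98.6% |
| 33 | 99.0% |
| 36 (no dropout) | 99.1% |

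**Step 3: power in one BMI group of 36.** After dropout, 36 × 0.9 = 32.4.

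| Evaluable in the stratum | Exact Fisher power, 80% vs 29% |
|---|---|
| 16 + 16 | 76.1% |
| 16 + 17, usual two-sided p-value | 83% to 84% |
| 16 + 17, p-value by doubling the smaller tail | 75% to 76% |
| 18 + 18 (no dropout) | 85.2% |

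The stated 80% lies inside this range. By the exact calculation a stratum would need 38, and two strata 76, so 72 is close to per-stratum sizing without matching it exactly.

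**Step 4: sensitivity of the 99%.** The Discussion says that the control group of the cited study did not undergo active calorie restriction as the guidelines advise, whereas the SOC arm here does. The 29% may then be too low. The documents give no better value, so 45% is taken purely as an illustration: at 80% vs 45% with 32 per arm, power is about 78%. Lowering the other rate instead, 65% vs 29% with 32 per arm gives about 79%.

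**The case against.** The best defence is that a target of 80% can be read as a minimum, which 72 more than meets. The error understates power, recruitment had closed by January 2023 according to Trial status, and no conclusion from the pooled test is endangered. All of this stands, and it is why the point is not graded higher. It does not explain the figure: a total nearly twice the 38 needed (72 / 38 = 1.9) is not what a calculation to 80% returns, and the article gives no other reason for it.

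A second defence is that the article does name its comparison, between the two treatment groups, and makes the strata subgroups. That is correct. Per-stratum sizing is therefore only an inference from the arithmetic and from the split into 36 and 36.

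A reader might go further and infer three things that the documents do not support:

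- *That the stated power is wrong on the stratum reading too.* The 76% depends on rounding 32.4 down to 32 and splitting it evenly. Other reasonable choices give up to 85%, so 80% is a fair rough figure for a stratum.
- *That two stratum tests would raise the false-positive rate to 9.75%* (1 − 0.95²). The article declares no such pair of confirmatory tests. The figure is also only a nominal bound, because Fisher's test is conservative here. Its actual size is at most 2.0% at 16 per arm and 2.9% at 18, so two such tests give at most 1 − 0.980² = 4.0% and 1 − 0.971² = 5.7%.
- *That 99% is the real power of the trial.* It holds only for the stated rates and for Fisher's test on responders. The statistical methods section lists t-tests and a linear mixed model, to which it does not apply.

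**Conclusion.** The concern holds for the comparison that the section names. With 80% vs 29%, a two-sided 5% Fisher's exact test and 10% dropout, 80% power needs 38 randomised, and 72 randomised gives 98.6% to 99.1%. That conclusion does not depend on rounding or on the choice between the exact and approximate methods.

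The likely origin, one calculation per BMI group that was then doubled, fits the numbers roughly (about 75% to 85% per stratum) but cannot be established from the article. Severity is moderate: the pooled comparison is not underpowered under the stated rates, and what needs repair is a figure that cannot be reproduced and an unstated basis for the total. The margin above 80% is not assured, because it rests on a 29% control rate from patients who were treated less actively than this SOC arm.

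**What to change.** Keep 72 and replace the justification, for example with:

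> The primary comparison is ICR versus SOC in all randomised patients. With 72 randomised and about 64 evaluable after 10% dropout, a two-sided 5% Fisher's exact test has about 99% power if the true responder rates are 80% and 29%. The control rate comes from a study without active calorie restriction; power is lower if the SOC arm does better (for example, about 78% at 80% versus 45% with 32 per arm). Thirty-six patients per BMI group give roughly 75% to 85% power within each group under the original rates. Results by BMI group are secondary.

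If the authors did size the trial per stratum, they should say so in the same paragraph as the reason for 72. The cost is one reworded paragraph, with no extra patients and no change to randomisation or data collection. The wording should be settled before the data are analysed.

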### Recruitment

The FLICR trial will recruit patients from Ewha Womans University Mokdong Hospital. This study will only recruit Korean patients. The Department of Nutritional Science and Food Management, Ewha Womans University, will collaborate with this study. The randomized allocation will be conducted at Ewha Womans University Mokdong Hospital. Eligible patients will be screened by the principal and sub-investigator (hepatologists) and will undergo screening to investigate whether they fulfill the eligibility criteria and none of the exclusion criteria for the study.

### Assignment of interventions: allocation

For eligible patients, the principal or sub-investigator will complete the patient enrollment form and enroll the patients. Patients will be randomly assigned to receive ICR or SOC by the enrolling investigator via a computer-generated randomization sequence using block randomization (block size = 6) with a 1:1 ratio and stratification by BMI (≥ 25 and < 25 kg/m^2^). After the participants have been assigned to the ICR or SOC group through the randomization procedure, they will be informed by the enrolling investigator.

